### Ethical Considerations

This study is in compliance with the Helsinki Declaration and local legislation. Ethical approval was sought and granted by the New Territories West Cluster Clinical & Research Ethics Committee on July 3, 2018, with Ref. No.: NTWC/CREC/18038 at Tuen Mun Hospital in Hong Kong. All participants signed an informed consent from the nurses before participating in the study. This study is noncommercial.

To protect the interest of vulnerable subjects, confidentiality will be ensured according to the guidelines from the Hospital Authority in Hong Kong. For example, the data, including personal information, will be stored in encrypted files during and after the study. The investigators will be responsible for the safekeeping of the personal data, and only they will have access to the personal data during and after the study. The data will be kept in a locked cabinet for 5 years after the study. After completion of this storage period, the data files will be destroyed.

## Results

This study is currently underway with funding support from the Hong Kong College of Family Physician Research Seed Fund 2017. Participants could start the study at different times. All testing was completed in mid-November 2019. The results of the study will then be communicated via publications.

## Discussion

### Impact

Demonstrating which of the two methods tested here is more effective can have a major impact on clinical practices when designing and proposing clinical protocols for the management of diabetes. Clinical interviewing skills and health education are the essential strategies used by nurses with their patients. Obtaining scientific evidence on the effectiveness of MI in primary care through strict monitoring of the training methods and controlling the integrity of the therapies applied will allow us to have economical, brief, effective, and applicable techniques to help patients change their health habits and achieve better health outcomes.

### Limitations

This study design has several limitations. First, as the resources for this study are limited, we will not be able to collect a large sample size. Consequently, it might be more difficult to identify statistically significant intervention effects. This issue highlights the importance of preventing dropouts from the intervention. Dropouts will be prevented by sending telephone reminders to participants for follow-ups. In addition, to test our hypotheses, participants will need to fill out many questionnaires, which may cause higher levels of attrition.

### Conclusions

This study is one of the first attempts to assess the extent that the MI approach helps in overall diabetic care. The results obtained will help us understand the practical effectiveness of this approach, including its limitations and actual impact on Chinese patients with diabetes. If this method proves to be effective, our intention is to disseminate and promote that intervention used in APN sessions to promote better self-management.

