**Objective:**

This study will obtain preliminary data on the impact of a nurse-led MI intervention in improving glycemic control, as well as clinical, psychosocial, and self-care outcomes for individuals with type 2 diabetes mellitus when compared with usual care, with the aim of improving diabetic control in patients with diabetes.

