### Objectives

This project aims to obtain preliminary data regarding the impact of MI on diabetes control compared with normal care among patients seen in primary care settings. The outcomes of interest include glycemic control (as measured by HbA_1c_), blood pressure, BMI, hip and waist circumference, fasting blood, and psychosocial and self-care measures.

The findings could inform the efficacy of MI for diabetes management in patients in family practices and contribute to better disease control.

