### Sample Size Calculation

Sample size estimates were calculated using the ﬁxed number of clusters (2) available to the current study. The intracluster correlation coefﬁcient (ICC) accounts for the greater similarity of responses in patients within clusters compared with between clusters, and we could apply an ICC of 0.05 as typical in primary care settings [29]. The effect size for the primary outcome, HbA_1c_, was anticipated to be 0.32%, based on findings from a published meta-analysis [29]. Using these parameters, a sample size calculator for cluster-randomized trials [29] could estimate a total number of samples that would be required to achieve a power of 80%, while maintaining an alpha of 5% and a participant attrition rate of 20%.

However, since this is a pilot study, we will deploy a convenient sampling of 20 to 25 samples in each arm depending on resources. We anticipate performing a pragmatic cluster RCT in the future when resources are available so that sample size can be calculated with adequate power.

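### The article ties dissemination of MI to this pilot showing effectiveness, which 20 to 25 patients in one clinic per arm cannot establish and which is not reconciled with the powered cluster trial it anticipates

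*Protocol article*

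**What the plan says.** On purpose and size, the article is modest. The abstract's Objective says "This study will obtain preliminary data on the impact of a nurse-led MI intervention in improving glycemic control", and the Objectives section says "This project aims to obtain preliminary data regarding the impact of MI on diabetes control compared with normal care". Under Sample Size Calculation, the ingredients of a power calculation are listed (ICC 0.05, 80% power, 5% alpha, 20% attrition, and an HbA1c effect that "was anticipated to be 0.32%, based on findings from a published meta-analysis"), but no required number is given. Instead, "we will deploy a convenient sampling of 20 to 25 samples in each arm depending on resources". Adequate power is placed in a later study: "We anticipate performing a pragmatic cluster RCT in the future when resources are available so that sample size can be calculated with adequate power". Limitations concedes that significant effects may be hard to detect with so few patients. Study Design and Recruitment Procedure make the clinic the unit of randomization, with two clinics and one per arm.

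On consequences, the article is bolder. The last section of the Discussion says that the results will show how effective the approach is in practice, and then: "If this method proves to be effective, our intention is to disseminate and promote that intervention used in APN sessions". The abstract's Conclusions promise scientific evidence on effectiveness, and Impact speaks of demonstrating which of the two methods works better. None of these three places mentions the later trial.

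**The concern.** The condition on roll-out stands in a paragraph about this study's own results, so the natural reading is that a favourable pilot would lead to dissemination. Effectiveness is not defined there. The only numerical threshold in the article is the P<.05 in Statistical Analysis, so a reader is likely to take a significant HbA1c difference as the proof meant.

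If so, a change in nurse-led diabetes care would rest on a comparison of two clinics. A chance difference between clinics could be read as an effect of MI, and the study that the article expects to have adequate power would appear only in a methods paragraph. What is at stake is what this trial may conclude and what its result is used for.

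**Working it through.** **Nothing to reproduce.** The 20 to 25 per arm is set by resources, and no SD or powered sample size is stated. The check therefore asks what a comparison of this size can show.

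**Inputs from the article.** n = 20 to 25 per arm; effect 0.32 HbA1c percentage points; ICC 0.05; one clinic per arm; alpha 5% (taken as two-sided).

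**Assumption.** SD of the HbA1c outcome 1.0 to 1.5 points. The article gives none. A normal approximation is used throughout, although the article plans nonparametric tests.

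**1. Standard error ignoring clustering.** SE = SD × √(2/n).
- SD 1.0, n = 25: 1.0 × √0.08 = 0.28
- SD 1.5, n = 20: 1.5 × √0.10 = 0.47

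The effect sought is 0.32, so it is about one standard error or less. The 95% interval has a half-width of 1.96 × 0.283 = 0.55 to 1.96 × 0.474 = 0.93.

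**2. Standard error with the article's ICC and one clinic per arm.** SE = SD × √(2 × (0.05 + 0.95/n)).
- SD 1.0, n = 25: √(2 × 0.088) = 0.42
- SD 1.5, n = 20: 1.5 × √(2 × 0.0975) = 0.66

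The clinic component alone is SD × √(2 × 0.05) = 0.32 at SD 1.0. A typical chance difference between two clinics is then as large as the whole anticipated benefit, and recruiting more patients in the same two clinics does not shrink it.

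**3. Power for 0.32.** Power ≈ Φ(0.32/SE − 1.96).

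| SD | n per arm | Ignoring clustering | With ICC 0.05 |
|---|---|---|---|
| 1.0 | 20 | 17% | 11% |
| 1.0 | 25 | 20% | 12% |
| 1.5 | 20 | 10% | 7% |
| 1.5 | 25 | 11% | 7% |

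These figures assume no dropout. At the 20% attrition in the article, 20 patients become 16, and power at SD 1.0 ignoring clustering falls to 15%. At a favourable SD of 0.8 it is still only 24% to 29% for n = 20 to 25 with clustering ignored.

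**4. True type I error of a nominal 5% test that ignores clustering.** Design effect = 1 + (n − 1) × 0.05; true error = 2 × (1 − Φ(1.96/√design effect)).
- n = 20: design effect 1.95; 1.96/1.396 = 1.40; error 16%
- n = 25: design effect 2.20; 1.96/1.483 = 1.32; error 19%

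This result needs no SD. With one clinic per arm, the between-clinic variance cannot be estimated from the trial's own data, so any allowance for it has to come from an assumed ICC.

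**The case against.** The strongest reply is that the closing sentence is a statement of intent in a Discussion. It has no threshold, no timetable and no link to P<.05, and its condition could be met by the later trial. The article is also open about the small sample. Much of this stands, and it rules out several stronger readings.

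- *That the article contradicts itself because the powered trial must come first.* A reader might infer this, but Sample Size Calculation says only "We anticipate performing a pragmatic cluster RCT in the future when resources are available". It sets no order and does not make that trial a condition of dissemination. The passages are unreconciled, not contradictory.
- *That there is a decision rule.* There is none; the sentence is not operational.
- *That a null result would end the programme.* The article is silent on a null result, and it makes the later trial depend on resources.
- *That progression criteria are missing.* A condensed article may leave these to the full protocol. Results also reports that testing was completed in mid-November 2019, so thresholds could no longer be set in advance. Retention would be too imprecise to sort into bands anyway: at 20% attrition, 40 of 50 retained has an exact 95% interval of 66% to 90%, and 20 of 25 has 59% to 93%.

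What does not stand is that the wording is harmless. The paragraph concerns this study's results, and two other places make the same claim about effectiveness.

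**Conclusion.** The point holds as one about what the article says its result will be used for. Dissemination is tied to effectiveness in the Discussion's Conclusions, with support from the abstract's Conclusions and from Impact. The Objective, Objectives, Sample Size Calculation and Limitations describe a study that cannot establish effectiveness.

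The anticipated effect is about one standard error or less before clustering is counted, and power is roughly 7% to 12% once it is. Both rest on an assumed SD of 1.0 to 1.5. The type I error of about 16% to 19% rests on the article's ICC of 0.05 and on a test that ignores clustering. The article names nonparametric tests and does not say whether clinics are allowed for, so that figure is conditional.

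The documents do not support going further, to a strict contradiction or a formal rule on roll-out or stopping.

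**What to change.** Reword the end of the Discussion's Conclusions along these lines: *The HbA1c comparison in this pilot is preliminary and will be reported as an estimate with an interval. It will inform whether and how to run the planned cluster randomized trial. Dissemination will await adequately powered evidence.* Align the abstract's Conclusions and Impact with this, so that neither says the pilot will demonstrate effectiveness, and carry the same wording into the results paper.

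State beside the interval that one clinic per arm leaves the clinic effect inseparable from the MI effect. If clustering is ignored, the interval is too narrow by a factor of 1.40 to 1.48 at ICC 0.05 (√1.95 to √2.20).

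Consent and 12-month retention may be reported descriptively where they were recorded, without pass/fail thresholds. Retention is useful for planning, since Limitations itself warns of a questionnaire burden "which may cause higher levels of attrition".

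The cost is wording in three places and, at most, counts from existing records. The downside is giving up a roll-out claim that this pilot cannot support.

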## Appendix

Multimedia Appendix 1 CONSORT-eHEALTH checklist (V 1.6.1).

## Abbreviations

APN: advanced practice nurse
C-DMSES: Chinese Diabetes Management Self-Efficacy Scale
DM: diabetes mellitus
GOPC: government outpatient clinic
HbA_1c_: glycated hemoglobin
ICC: intracluster correlation coefficient
K10: Kessler 10
MI: motivational interviewing
MITI: Motivational Interviewing Treatment Integrity
NLC: nurse-led clinic
QOL: quality of life
RCT: randomized controlled trial
SDSCA: Summary of Diabetes Self-Care Activities.
